## 3. Discussion

The RESPONSIBLEPLAY^©^ intervention, grounded in the Multi-theory Model (MTM) of health behavior change, offers a novel and comprehensive approach to addressing gambling-related issues among college students. By integrating the constructs of MTM, such as behavioral confidence, social support, emotional transformation, and changes in physical and social environments, this protocol is designed to address not only the knowledge gaps but also the underlying psychological and behavioral factors that drive gambling habits. It is envisaged that this approach will lead to more sustainable behavior change and better long-term outcomes for participants than traditional knowledge-based interventions, which often focus solely on increasing awareness without addressing the emotional, social, and environmental aspects of behavior change. As such, this intervention represents a significant advancement over conventional methods by offering a tailored, theory-driven framework that targets both the initiation and maintenance of responsible gambling behaviors.

### 3.1. Significance and Implications

This study addresses a critical gap in the literature by applying MTM constructs to promote responsible gambling behaviors among college students. Unlike knowledge-based interventions that often focus solely on raising awareness without facilitating lasting behavioral change, the MTM-based approach incorporates actionable strategies that aim to not only initiate but also sustain changes in gambling behavior. Through activities such as photovoice, journaling, and role-playing, the participants are equipped with practical tools to recognize, plan for, and maintain responsible gambling habits. These hands-on strategies encourage active participation and empower individuals to take ownership of their behavior, fostering long-term outcomes.

The anticipated outcomes of the RESPONSIBLEPLAY^©^ intervention include improvements in Problem Gambling Severity Index (PGSI) scores and enhanced MTM construct scores, thus validating the framework’s effectiveness for addressing gambling-related issues. By integrating both theoretical and practical components, the intervention ensures it can be adapted for diverse populations, settings, and types of gambling behaviors. For instance, strategies like limiting physical access to gambling opportunities or fostering peer support networks are flexible and applicable across various cultural and socioeconomic contexts, making the RESPONSIBLEPLAY^©^ intervention a potentially scalable and sustainable solution for addressing gambling issues on a broader scale.

### 3.2. Limitations

While this study introduces a robust framework for promoting responsible gambling behaviors, several limitations must be acknowledged regarding its implementation. First, the reliance on a convenience sample from a single southwestern university may limit the generalizability of the findings. The specific gambling behaviors and environmental influences experienced by the participants may not fully represent those of college students in other regions or demographics. To enhance the external validity of this study, future research should aim to replicate this study across diverse populations and settings to better assess its broad applicability. Additionally, the participants who complete all sessions and follow-up assessments may represent a more motivated or problem-aware subgroup, which could introduce interpretive bias. To address this concern, we will compare baseline characteristics between completers and non-completers to assess the presence of any systematic differences and report these findings transparently in future publications.

This study’s three-week intervention period, although consistent with similar behavior change interventions, may not fully capture the long-term sustainability of responsible gambling behaviors. The eight-week follow-up provides some insight into short-term changes; however, extended longitudinal studies are needed to evaluate the persistence of behavior change and the intervention’s capacity to prevent relapse over time.

Participant attrition remains a significant concern in multi-session interventions, particularly within college populations. While we increased the initial sample size by 50% to accommodate the expected dropout, we acknowledge that actual attrition may exceed this estimate. To address this, we have incorporated several retention strategies, including flexible scheduling, frequent reminders (via email), and graduated incentives to encourage session attendance and follow-up completion. We will transparently report attrition rates at each study phase and perform sensitivity analyses comparing baseline characteristics between completers and non-completers. This will help assess whether retention introduces systematic bias—particularly the concern that the participants who complete all the sessions may represent a more motivated or problem-aware subgroup. These insights will be critical in informing the design and scalability of future studies.

This study relies on the PGSI as one of the key outcome measures. While the PGSI is a widely validated and commonly used instrument, its 12-month recall period may limit its sensitivity to detecting short-term behavioral changes resulting from the intervention. To address this, we will supplement our analyses with MTM construct scores, which are specifically designed to measure short-term behavioral initiation and sustenance. Additionally, we will conduct item-level analyses of the PGSI responses (e.g., related to gambling expenditure, time lost, or emotional impact) to assess whether certain dimensions demonstrate greater sensitivity to short-term change. While the PGSI was selected for its classification utility and comparability across studies, we acknowledge that it is best suited for long-term assessments. Accordingly, we are also exploring the feasibility of a 6- to 12-month follow-up study to better align with the PGSI’s recall window and to assess sustained changes in gambling behavior. This extension will depend on participant retention and funding availability but would provide a more complete evaluation of the intervention’s longitudinal impact.

While simple randomization is used for group assignment, we acknowledge that this method may result in imbalances in baseline characteristics, particularly in smaller samples. Although reproducibility was ensured through the use of a fixed seed in SAS, future studies may benefit from using stratified or block randomization to enhance group comparability.

Lastly, the self-reported nature of gambling behaviors, while necessary for understanding personal habits and attitudes, introduces the potential for recall and social-desirability biases. The participants may underreport or overreport their gambling behaviors due to memory lapses or the desire to present themselves in a more socially acceptable light. To address these biases, future studies could incorporate objective measures or third-party reports to provide a more accurate assessment of gambling behaviors and the intervention’s impact.

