### 2.3. Sample Size Calculation

A power analysis was conducted using G*Power (version 3.1) [18] to estimate the required sample size for this study. Based on a Two-Way Mixed Analysis of Variance (ANOVA) with a medium effect size of 0.30, two intervention groups, three time points (pre-, post-, and follow-up), an alpha level of 0.05, and a beta of 0.20 (80% power), the analysis assumed a correlation of 0.5 among repeated measures and applied a non-sphericity correction of 1. The calculation indicated a required sample size of 20 participants per group. To account for potential attrition and missing data, the sample size was increased by 50%, resulting in a total of 60 participants, with 30 in each group.

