### 2.11. Per-Protocol Analysis

A per-protocol (PP) analysis may be conducted to evaluate the efficacy of the RESPONSIBLEPLAY^©^ MTM-based intervention under optimal conditions [21]. This analysis includes only those participants who fully comply with the intervention protocol and complete the follow-up assessments. By focusing on this subset of participants, the PP analysis aims to provide a more precise estimate of the intervention’s efficacy. Participants will be included in the PP analysis if they meet the following criteria:Absence of Major Protocol Violations: The participants must strictly adhere to the predefined inclusion criteria and avoid any significant deviations from the study protocol [21].Completion of Prescribed Intervention: Only participants who complete their assigned intervention as designed must be considered [21].Availability of Primary Outcome Data: The participants must have complete data for the primary outcome measure to be included in the analysis [21].

The per-protocol (PP) analysis seeks to confirm the efficacy of the interventions by excluding participants who fail to adhere to the protocol or do not complete this study. This approach ensures that the observed effects can be directly attributed to the interventions, focusing only on the participants who fully comply with the study design. In contrast, the intention-to-treat (ITT) analysis includes all randomized participants, regardless of their adherence to the protocol, providing a more conservative estimate of treatment efficacy. Together, these complementary methods offer a comprehensive view of the intervention’s impact under both optimal and real-world conditions [21].

The decision to conduct only a PP analysis is based on the goal of evaluating the intervention’s efficacy under ideal conditions, where adherence to the protocol is maximized. By focusing exclusively on the participants who strictly follow the study protocol, the PP analysis eliminates the confounding effects of non-adherence or protocol deviations. This approach provides a clearer understanding of the potential benefits of the RESPONSIBLEPLAY^©^ MTM-based intervention. It is particularly suitable for assessing health behavior interventions, as the impact of such interventions can be more accurately observed in a population that fully adheres to the prescribed protocol [21].

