### 2.13. Inferential Statistical Methods

This study utilizes the following inferential statistical methods to evaluate the intervention’s impact as indicated in Table 3:Two-Way Mixed Analysis of Variance (ANOVA): The repeated measures analysis will be used to assess mean differences over time (pre-test, post-test, follow-up) within subjects and between the experimental and comparison groups. This test will be applied to evaluate changes in PGSI scores and MTM construct scores across the three-time points, capturing both within-subject effects (e.g., changes over time) and between-group effects (e.g., differences between the experimental and comparison groups due to the intervention) [23]. This approach allows for a thorough understanding of how the participants’ gambling behaviors and MTM constructs evolve during the course of the intervention, while accounting for the repeated nature of the measurements.Mixed Analysis of Covariance (ANCOVA): If significant baseline differences are identified in key variables (e.g., PGSI scores, MTM construct scores, or demographic factors like age or gender), an ANCOVA will be incorporated into the model to control for these differences. For instance, if the participants in one group have significantly higher baseline PGSI scores, the ANCOVA will adjust for this disparity, ensuring that the observed effects on responsible gambling behavior are attributable to the intervention rather than to pre-existing variations between groups [23]. This statistical approach enhances the precision of the findings by accounting for baseline differences, allowing for a more accurate assessment of the intervention’s impact.

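### The baseline comparison of completers with non-completers, offered as the sensitivity analysis for attrition, re-estimates no effect: it cannot correct attrition bias and cannot reliably detect it

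*Protocol article*

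**What the plan says.** Section 2.11 (Per-Protocol Analysis) restricts the efficacy analysis: "This analysis includes only those participants who fully comply with the intervention protocol and complete the follow-up assessments". It adds a data condition: "The participants must have complete data for the primary outcome measure to be included in the analysis". The section opens by treating the per-protocol analysis as optional and describes intention-to-treat as complementary, but it closes by justifying "The decision to conduct only a PP analysis". Nothing stated elsewhere brings the excluded participants back.

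Section 2.13 (Inferential Statistical Methods) names a two-way mixed ANOVA: "This test will be applied to evaluate changes in PGSI scores and MTM construct scores across the three-time points". ANCOVA enters only if significant baseline differences are found.

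Section 3.2 (Limitations) calls attrition a significant concern that may exceed the allowance. It promises retention measures, reporting of attrition at each phase, and to "perform sensitivity analyses comparing baseline characteristics between completers and non-completers". The stated purpose is: "This will help assess whether retention introduces systematic bias". No split by arm is stated.

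**The concern.** A sensitivity analysis for missing data repeats the estimate of the treatment effect under a different assumption about the people who left. A table of baseline characteristics does not do this. It shows whether leavers differed from stayers at entry. Bias in a two-arm contrast comes mainly from different kinds of people leaving each arm, or from people leaving because of how they responded.

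The complete-data rule makes this matter. A participant with pre-test and post-test PGSI but no follow-up is discarded, although the post-test carries information about response.

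Dropout that differs by arm is plausible on the article's own facts. Section 2.7 states a USD 20 card after each session and again at follow-up in its account of the experimental arm; for the comparison arm it states only one card, at follow-up. Section 2.4 sends additional reminders to the experimental arm only. If the baseline comparison is the evidence that retention did no harm, it can reassure when there is bias and alarm when there is none.

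**Working it through.** **1. Expected loss.** Section 2.3 gives 20 per group, 40 in all, raised by 50%: 40 × 1.5 = 60. The allowance therefore covers a loss of 20/60 = 33.3%, leaving 40 completers and 20 non-completers. The 20 per group is taken as given here; this point does not depend on it.

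**2. Power of the baseline comparison at 40 v 20.** Two-sided t-test, alpha 0.05, df = 58, critical value 2.002. Noncentrality = d × √(40 × 20/60) = d × 3.651.
- d = 0.5 SD: noncentrality 1.826, power 43%.
- d = 0.3 SD: noncentrality 1.095, power 19%.

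**3. Does a flag track bias?** Simulation with 30 per arm, three time points, unit SD, correlation 0.5 (section 2.3), no true effect, about 33% dropout, 4,000 trials per row. Bias is in the baseline-to-follow-up change, experimental minus comparison; negative favours the experimental arm because a lower PGSI is better. Type I error is for the complete-case mixed-ANOVA interaction. The dropout mechanisms, and the logit slope of 1.5 where dropout is not random, are assumptions.

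| Assumed dropout | Bias (SD) | Type I error | Baseline test flags |
|---|---|---|---|
| Random in both arms | about 0 | 5% | 4.5% |
| On baseline only, same in both arms | about 0 | 5% | 99% |
| Experimental arm: on change score; comparison random | −0.37 | 16% | 16% |
| Experimental arm: on follow-up given baseline; comparison random | −0.32 | 13% | 5.0% |
| As the row above, with opposite sign in the comparison arm | −0.63 | 45% | 5.1% |

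In the last two rows the flag rate stays at 5% to 6% with 3,000 per arm, so a larger trial would not help. The second row is the converse: near-certain flagging with no bias in the contrast.

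**4. A milder mechanism.** 30 per arm, correlations 0.7 (pre/post), 0.5 (pre/follow-up) and 0.6 (post/follow-up), about one third missing follow-up, no true effect. Dropout is tied to a poor post-test score in the experimental arm only.
- Complete-case, baseline-adjusted: about 0.08 SD favouring the experimental arm at logit slope 1 per SD (standard error about 0.28 SD, type I error about 6% to 6.5%). Across slopes 1 to 3, 0.07 to 0.13 SD.
- Complete-case, unadjusted change: 0.02 to 0.05 SD in the opposite direction.
- Likelihood estimator using all available data (post-test on arm and baseline; follow-up on arm, baseline and post-test): 0.00 to 0.01 SD.
- Baseline t-test flags roughly 18% to 45% of trials over the same slopes.

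**The case against.** The strongest reply has four parts.

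*The comparison is not blind.* A reader might infer that it can never detect attrition bias. That is too strong. Where dropout tracks something correlated with baseline, it gives a partial signal: 16% in step 3 and 18% to 45% in step 4, against 5% by chance. It is a weak and unreliable detector. Even a flag shows selection, not bias in the group contrast.

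*The arms may not be pooled.* A reader might infer that the comparison lumps the arms together. Section 3.2 does not say so; it is silent on the split. Only the silence can be noted.

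*The effect may be small, or absent.* A reader might infer that the planned estimate is biased, by 0.08 SD. The documents do not support that. Random dropout, and baseline-driven dropout equal in both arms, give none. The 0.08 SD is under a third of its standard error and belongs to a baseline-adjusted analysis, which section 2.13 makes conditional; it does not describe the default mixed ANOVA. The larger figures come from dropout tied to unobserved follow-up values at an assumed strength.

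*A condensed article may leave missing-data methods to an analysis plan.* This would stand if the article were merely silent. It is not: it fixes a per-protocol, complete-data analysis and gives a baseline table the name and purpose of a sensitivity analysis.

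It also stands that section 3.2 is candid that completers may be more motivated, promises attrition rates by phase, and sets no rule that a non-significant comparison clears the result.

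**Conclusion.** The point holds in this form. As stated, the plan analyses only compliers with complete data, and the sensitivity analyses it names for attrition leave the effect estimate untouched. That they cannot correct bias is certain. That they cannot reliably detect it rests on 43% and 19% power at 40 v 20, and on simulations in which flagging ranged from chance level under substantial bias to 99% under none.

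The size and direction of any actual bias are unknown. They depend on the model and on a dropout mechanism that the article does not give: from none, through 0.08 SD favouring the experimental arm (baseline-adjusted) or 0.02 to 0.05 SD the other way (unadjusted change), to 0.3 SD or more if dropout follows unobserved response in one arm. That spread is the reason to re-estimate the effect under stated alternatives. The plan should be changed, although nothing here shows that the trial's result will be wrong.

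**What to change.** 1. Estimate the efficacy contrast with a likelihood-based repeated-measures model (PROC MIXED, unstructured covariance, baseline PGSI as covariate) in all randomised participants with any post-baseline survey. State this in section 2.13 and bring section 2.11 into line.
2. Make the sensitivity analysis a re-estimation of that contrast, with dropouts' follow-up values shifted by increasing amounts, separately by arm, until the conclusion changes. This is needed because the likelihood model alone does not address dropout driven by unobserved outcomes.
3. Keep the comparison of completers with non-completers, shown by arm, as description only. Remove from section 3.2 the label of sensitivity analysis and the claim that it assesses systematic bias.

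The cost is a little more analysis work in SAS 9.4, which section 2.10 already specifies. No new data are needed.

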### 2.4. Study Procedure

Participant recruitment will target college students aged 21 and older at the university. The recruitment efforts will include email invitations that introduce this study and invite eligible students to participate. The intervention sessions will be conducted in person. The participants will be randomly assigned to either the experimental group (RESPONSIBLEPLAY^©^: MTM-based intervention) or the comparison group (knowledge-based intervention) using SAS PROC SURVEYSELECT. Participant data will first be imported from an Excel file, and each participant will be assigned a unique ID. Simple random sampling (SRS) will then be conducted using PROC SURVEYSELECT, ensuring equal probability of assignment to either group. A fixed seed (12345) will be used to ensure reproducibility. The function will generate a selection indicator (Selected = 1 for the experimental group and Selected = 0 for the comparison group), which will be used to assign the participants accordingly. The final randomized dataset, including group assignments, will then be exported for implementation.

The intervention will be conducted over three weeks, with one session scheduled per week. Each session will span three days, offering multiple time slots to accommodate the participants’ schedules. This approach ensures that all the participants receive the same intervention content while allowing flexibility in attendance. The first session (Week 1) will include an orientation, completion of the pre-intervention survey, and the start of the intervention activities. The final session (Week 3) will consist of intervention activities followed by the post-intervention survey.

To enhance attendance and engagement, the participants will receive email reminders before each session. Additional reminders will be sent to the experimental group between sessions and after the intervention to reinforce the practice of responsible gambling behaviors. At the eight-week follow-up, the participants will attend a final assessment session, which will be scheduled in advance. Email reminders will also be sent to maximize participation.

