### 2.9. Instrumentation

The survey tool for this research consists of a 54-item questionnaire (Supplement S4) specifically designed and refined through a meticulous two-stage review process conducted by a panel of six experts. These specialists, with expertise in MTM theory, instrumentation, and the target population, evaluated the questionnaire’s face and content validity in two rounds. They assessed the clarity, readability, and relevance of the items, leading to wording adjustments and the removal of one item from the behavioral confidence section. Following these revisions, the panel reached a unanimous agreement on the adequacy of the content and face validity for each MTM subscale. The finalized instrument achieved a Flesch Reading Ease score of 57.4 and a Flesch–Kincaid Grade Level of 8.7, confirming its suitability for the intended audience. In prior studies utilizing this MTM-based instrument among college populations, internal consistency estimates (Cronbach’s alpha) for the subscales ranged from 0.76 to 0.89, indicating acceptable to strong reliability [11].

Participants in this study must complete the 54-item survey based on the Multi-theory Model (MTM) at three time points: before the intervention (pre-test), immediately after the intervention (post-test), and during the follow-up period at eight weeks post-intervention. Prior to participation, all individuals will be required to provide informed consent by signing a consent form. This ensures that the participants understand the purpose of this study, their role, and their rights, including confidentiality and voluntary participation.

The initial questions of the survey focus on the frequency and types of gambling activities the participants had engaged in over the past 30 days. These questions are essential for establishing baseline measurements and serve as screening criteria for this study. The participants are asked to report the number of days they gambled during this period and to specify the types of gambling activities they participated in, such as lotteries, sports betting, poker, and online gambling. This information helps to categorize the participants based on their gambling behavior and ensures that the sample includes individuals who are actively engaged in gambling.

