After the baseline questions, the survey includes the Problem Gambling Severity Index (PGSI) to assess the impact of gambling on various aspects of the participants’ lives over the past 12 months. This section consists of nine questions designed to evaluate the severity of gambling-related issues by examining factors such as financial strain, emotional distress, health complications, and social consequences linked to gambling behaviors. The participants rate their experiences on a scale from 0 (“Never”) to 3 (“Almost always”), providing a detailed measure of the extent to which gambling has affected their lives. This information helps classify participants as low-risk, moderate-risk, or problem gamblers based on their responses. The Problem Gambling Severity Index (PGSI) is a widely used and validated measure of gambling-related risk and severity. As a part of the Canadian Problem Gambling Index, it is commonly used in both general and college populations. The PGSI has demonstrated strong internal consistency in previous studies, with reported Cronbach’s alpha values typically ranging from 0.84 to 0.91, supporting its reliability as a measure of gambling-related risk behaviors [20].

The third section of the survey consists of 32 questions aimed at assessing the constructs of the Multi-theory Model (MTM) for both the initiation and sustenance of behavior change. These questions explore the participants’ readiness to initiate responsible gambling behaviors and the strategies they employ to maintain these behaviors over time. By focusing on the psychological, social, and environmental factors that influence behavior change, this section provides valuable insights into participants’ motivation, confidence, and commitment to adopting and sustaining responsible gambling practices. The final section of the survey collects demographic information, such as age, gender, and educational background, ensuring a thorough understanding of the participant population and enabling more accurate data analysis.

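### The only gambling measure in the planned analysis looks back 12 months but is read about 2 and 10 weeks after session 1, so it is unlikely to show a short-term effect; the 30-day item already in the survey is left out

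*Protocol article*

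**What the plan says.** Section 2.9 (Instrumentation) gives the PGSI as nine items, each rated 0 to 3, used "to assess the impact of gambling on various aspects of the participants’ lives over the past 12 months". The full 54-item survey is completed at pre-test, post-test and eight weeks post-intervention.

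Section 2.4 (Study Procedure) sets the timing: "The intervention will be conducted over three weeks, with one session scheduled per week". The pre-test is part of the Week 1 session, and the post-test closes the Week 3 session.

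On the role of the score, section 3.2 (Limitations) states: "This study relies on the PGSI as one of the key outcome measures". Section 2.13 says of the two-way mixed ANOVA: "This test will be applied to evaluate changes in PGSI scores and MTM construct scores across the three-time points". Table 3 names the same two outcomes, and section 3.1 expects PGSI scores to improve.

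Section 3.2 admits that "its 12-month recall period may limit its sensitivity to detecting short-term behavioral changes resulting from the intervention" and that the index suits long-term assessment best. It offers three responses:
- MTM construct scores as a supplement.
- Item-level work: "we will conduct item-level analyses of the PGSI responses".
- A follow-up at 6 to 12 months, whose feasibility is being explored and which depends on retention and funding.

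The survey opens with questions on the past 30 days: "The participants are asked to report the number of days they gambled during this period". Section 2.9 gives these a baseline and screening role. They do not appear in section 2.13 or Table 3.

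**The concern.** A score that sums up a year of gambling changes slowly when only the last few weeks of that year can differ between arms. Most of what the PGSI records at post-test and follow-up happened before session 1, and neither arm can alter it.

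Two consequences follow. A null PGSI result could mean that the programme does not work, or that the instrument could not yet register a change, and the trial could not tell these apart. Meanwhile the MTM scores do not suffer from this dilution. The stated objective in section 2.10 is efficacy in promoting responsible gambling behaviours, so a claim about behaviour could end up resting on readiness, confidence and self-reported strategies, which are what the experimental sessions teach.

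The disclosure does not settle this, because none of the three responses provides a gambling measure with a suitable window. Item-level analyses reuse the same items and the same 12 months. MTM scores are not a measure of gambling itself. The longer follow-up is not committed.

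**Working it through.** **1. The plan's own power figure.** Section 2.3 gives effect size 0.30, two groups, three time points, alpha 0.05, 80% power, correlation 0.5 and non-sphericity 1, and arrives at 20 per group. I read 0.30 as Cohen's f and use the G*Power default for the group-by-time interaction: lambda = f² × N × 3 / (1 − rho), with df 2 and 2(N − 2).
- N = 20 in total gives 81.2% power; N = 40 gives 98.8%; N = 60 gives more than 99.9%.
- So the inputs reproduce 20 in total, not 20 per group. That is a separate matter; it makes the trial larger than its inputs require.
- Section 2.3 does not say which outcome the 0.30 refers to, and makes no allowance for the recall window.

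**2. Share of the window after session 1.** Three weekly sessions put the post-test about 2 weeks after session 1 (3 if whole weeks are counted). Follow-up is 8 weeks later, at 10 or 11 weeks. Take 12 months as 52 weeks.
- Post-test: 2/52 = 3.8%, 3/52 = 5.8%. Before session 1: 96.2% or 94.2%.
- Follow-up: 10/52 = 19.2%, 11/52 = 21.2%. Before session 1: 80.8% or 78.8%.

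**3. Illustration of size.** The document gives no PGSI mean or SD. Assume a mean of 6, an SD of 3 to 5, answers that track the window proportionally, complete cessation in one arm and no change in the other.
- Fall at post-test: 6 × 2/52 = 0.23 to 6 × 3/52 = 0.35 points.
- Fall at follow-up: 6 × 10/52 = 1.15 to 6 × 11/52 = 1.27 points.
- Follow-up difference in SD units: 1.15/5 = 0.23 to 1.27/3 = 0.42.

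The interaction f is half the standard deviation (divisor 3) of the three between-arm differences, in SD units. With rho = 0.5:

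| Weeks after session 1 | SD | Differences (pre, post, follow-up) | f | Power, N = 40 | Power, N = 60 |
|---|---|---|---|---|---|
| 2 and 10 | 5 | 0, 0.046, 0.231 | 0.050 | 9.6% | 12.1% |
| 2 and 10 | 3 | 0, 0.077, 0.385 | 0.083 | 18.7% | 26.6% |
| 3 and 11 | 5 | 0, 0.069, 0.254 | 0.054 | 10.3% | 13.3% |
| 3 and 11 | 3 | 0, 0.115, 0.423 | 0.089 | 21.0% | 30.2% |

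Pairing 0.42 SD with a post-test difference one fifth as large gives about 31% at N = 60.

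**4. How far this moves with the assumptions.**
- Correlation: the windows overlap heavily (50/52 = 96% between pre-test and post-test, 42/52 = 81% between pre-test and follow-up), which may raise rho. At rho = 0.9 the same four cases give 31 to 78% at N = 40 and 45 to 93% at N = 60.
- Mean/SD ratio: the cases above use 6/5 = 1.2 to 6/3 = 2. A ratio of 3 gives 3 × 10/52 = 0.58 SD at follow-up, f = 0.125, and power of 38% (N = 40) or 54% (N = 60) at rho = 0.5.
- Benchmark: a difference that is equal at post-test and follow-up is detectable with 80% power, at rho = 0.5, from about 0.87 SD (N = 40) or 0.70 SD (N = 60).

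**5. Window of the item not used.** The eight-week follow-up is 56 days after session 3, so a 30-day window begins on about day 26 after it and lies wholly after the programme. At pre-test the window lies wholly before it. At post-test about 14 of the 30 days follow session 1, so that reading is mixed and follow-up is the clean one.

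**The case against.** The protocol states this limitation itself and offers three responses, one of which, the 6- to 12-month follow-up, is aimed directly at the recall window. That deserves credit. It remains contingent, so it does not make the committed readings more informative.

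A reader might infer that the PGSI cannot show the assumed effect. The documents do not support that. The items are ordinal ratings from never to almost always, and nothing says how respondents weigh recent weeks; if recent experience dominates, the dilution is smaller. The 0.30 is not tied to the PGSI. Setting the illustrated 0.23 to 0.42 SD against the 1.27 SD that f = 0.30 implies (0.30 / 0.2357, for a constant difference after baseline) would overstate the gap, because 1.27 SD is the assumed effect and not the smallest detectable one. At rho = 0.9 some full-cessation cases reach good power. All this stands, and it limits the point to unlikely rather than impossible. Complete cessation is, however, an extreme case for a programme that promotes responsible gambling, so real differences would tend to be smaller than those illustrated.

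A reader might also infer that a PGSI change at post-test could only be response bias. That does not follow: dilution pulls the contrast towards zero and does not by itself create a false positive. Self-report bias is disclosed separately in section 3.2.

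The MTM section also asks about strategies used to maintain behaviour, so it is not devoid of behavioural content. It still does not measure gambling.

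Finally, gambling days are not the target. Section 2.2 links moderate-risk scores to exceeding budgets, losing track of time and guilt, and someone can gamble as often but within limits. This is a good reason not to make days gambled the primary outcome.

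**Conclusion.** The point holds in a limited form. The timing follows from the protocol alone: 94 to 96% of the post-test window and 79 to 81% of the follow-up window precede session 1. Given respondents who apply the window as worded, the PGSI is unlikely to show a short-term effect, and a null result on it would be hard to interpret. The disclosed remedies do not supply a gambling measure whose window fits the readings, while one that does at follow-up sits unused in the survey.

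The power figures of about 10 to 30% are illustrative. They rest on an assumed mean and SD, proportional recall, complete cessation against no change, and rho = 0.5; they rise with rho or with a larger mean/SD ratio. They do not show that the trial must fail on the PGSI, and the argument does not touch the power for MTM scores.

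**What to change.** - In section 2.13 and Table 3, pre-specify past-30-day gambling days at the eight-week follow-up as a behavioural outcome beside the PGSI, adjusted for its pre-test value whether or not the arms differ at baseline. Confirm in section 2.9 that the item is asked at all three surveys, as the description of the full survey implies.
- Describe the MTM scores as mechanism outcomes, and state that a claim of efficacy on gambling behaviour will not rest on them alone.
- In section 2.3, state which outcome the 0.30 refers to and that it is not justified for the 12-month PGSI.
- Keep the PGSI for screening and as an outcome.

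Cost: no new data collection if the item is repeated as described, but one more outcome to analyse and report, and an update to the registration of a trial that is already underway. Gambling days capture frequency and not the whole of responsible gambling, so the item should support the PGSI rather than replace it as primary.
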